| Number of participants:
A minimum of ten up to a maximum of 20 FRDA participants will participate in each part of the study.                                                                                                                                                                                                                                                                                                                                                                                                                                                                                                                                                                                                                                                                                                                                                                                                                                                                                                                                                                                                                                                                                                                                                                                                                                                                                                                                                                                                                                                                                                                                                                                                                                   |                                                                                                                                                                                                                                                                                                                                                                                                                                                                                                                                                                                                                                                                                                                                                                                                                                    |

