### 1) Single dose escalation study, Part I

Firstly, we will treat the participants with a single dose of 2g of nicotinamide given orally in tablet form. We will measure the FXN levels before treatment and at 2 ( $\pm$  15 mins), 4 ( $\pm$  25mins), 8 ( $\pm$  1hr) and 24 ( $\pm$  2.5hrs) hours after treatment on separated peripheral blood lymphocytes. Plasma will be stored so that nicotinamide concentrations can be assessed by high-performance liquid chromatography (HPLC) as previously described (Stratford et al., 1992). In addition, chromatin will be extracted and stored at  $-80^{\circ}\text{C}$ . In the absence of FXN upregulation we will escalate the dose following a 'flushing out' period of at least one week. We will escalate by 2g increments to 6g and then 1g increments to a maximum of 8g until FXN upregulation is achieved and in the absence of AEs that, in the opinion of the Chief Investigator (CI) or his delegated doctors, may put the safety of the participant at risk. At 8g of nicotinamide we expect that some participants might experience nausea. Participants will be assessed throughout for nausea using a visual analogue scale (VAS). Those with significant nausea will be offered anti-nausea treatment (typically metoclopramide or domperidone) to avoid vomiting. In the event of vomiting occurring, intravenous (IV) fluid will be given as required.

A minimum of ten participants will be recruited in this part of the study according to the schema shown in the table below. Two participants per visit will receive no nicotinamide. This will allow within-participant comparisons and control for the study procedures. The dose escalation will cease when we have reached the maximum tolerated dose (MTD), at least 5-fold upregulation in 50% of participants, or 8g nicotinamide, whatever comes first.

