**Table 1: Recruitment schema for Part I**

|                | Visit 1 | Visit 2 | Visit 3 | Visit 4 | Visit 5 |
|----------------|---------|---------|---------|---------|---------|
| Participant 1  | D1      | D2      | D3      | D4      | No      |
| Participant 2  | D1      | D2      | D3      | D4      | No      |
| Participant 3  | D1      | D2      | D3      | No      | D5      |
| Participant 4  | D1      | D2      | D3      | No      | D5      |
| Participant 5  | D1      | D2      | No      | D4      | D5      |
| Participant 6  | D1      | D2      | No      | D4      | D5      |
| Participant 7  | D1      | No      | D3      | D4      | D5      |
| Participant 8  | D1      | No      | D3      | D4      | D5      |
| Participant 9  | No      | D2      | D3      | D4      | D5      |
| Participant 10 | No      | D2      | D3      | D4      | D5      |

No = No treatment

D1 = 2g of Nicotinamide

D2 = 4g of Nicotinamide

D3 = 6g of Nicotinamide

D4 = 7g Nicotinamide

D5 = 8g of Nicotinamide , Maximum Tolerated Dose (MTD) or dose found in visits 1-4 capable of upregulating FXN by at least 5-fold.

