#### 4.5. Exclusion Criteria for the interventional study

1. Participants with significant clinical dysphagia.
2. Participants taking Sodium Valproate or any other known histone deacetylase inhibitor.
3. Participants taking part in another interventional clinical trial or who have done so within 30 days before screening.
4. Participants known to be positive for human immunodeficiency virus (HIV).
5. Participants with any additional medical condition or illness that, in the opinion of the CI would interfere with study compliance and/or impair the participant's ability to participate or complete the study. Concurrent diseases or conditions that may interfere with study participation or safety include liver disease, bleeding disorders, arrhythmias, organ transplant, organ failure, current neoplasm, poorly controlled diabetes mellitus, poorly controlled hypertension, clinically significant haematological or biochemical abnormality.
6. Patients with a history of substance abuse (e.g. alcohol or drug abuse) within the previous 6 months before enrolment.
7. Participants with a history of severe allergies.
8. Female participants who are lactating or pregnant (positive pre-randomisation serum pregnancy test) or plan to become pregnant during the study.
9. Hypersensitivity to Nicobion (nicotinamide) or any of the excipients in this preparation
10. Liver function tests outside the normal range: aspartate aminotransferase (AST), alanine aminotransferase (ALT), bilirubin which in the opinion of the CI would put the participant's safety at risk.

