#### **7.9. Single Dose Escalation Visits**

At each visit, participants will return to the Imperial CRF to receive treatment with nicotinamide. They will be admitted to the Imperial CRF and the following assessments will be performed:

- Vital signs assessment (pulse rate, blood pressure, respiration rate, pulse oximetry and temperature), these will be repeated prior to each blood sample being taken (see below).
- Assessment and recording of AEs since baseline throughout the visit
- Review of concomitant medications
- If participants experience nausea they will be given a VAS to rate the severity.
- Each participant will be given an oral dose of nicotinamide (as detailed in schema).
- Blood samples taken for standard clinical laboratory tests (haematology, chemistry, and LFTs), blood glucose will be measured using a BM stick at predose and 24 hours following nicotinamide administration.
- Blood samples to assess FXN level will be taken predose and at 2 ( $\pm$  15 mins), 4 ( $\pm$  25mins), 8 ( $\pm$  1) and 24 ( $\pm$  2.5) hours following nicotinamide administration.
- On the last dosing visit blood samples for the separate Chromatin immunoprecipitation studies will be taken at pre-dose and at 8 ( $\pm$  1) hours post-dosing.
- Participants will spend the day within the Imperial CRF and return home after the last blood test. They will return the following day for the 24 hour blood test. In some cases, if travel is difficult, participants may be offered overnight accommodation either at the Imperial CRF or private accommodation.
- All participants will be reviewed by the CI or delegates prior to discharge.

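### Part I places participants in the rows of Table 1 by participant number, with no random or concealed step, so who is untreated at which visit, and which two miss the D5 column, could be chosen

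*Protocol*

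**What the plan says.** Section 4.1, under the Part I heading, states that "A minimum of ten participants will be recruited in this part of the study according to the schema shown in the table below". The table, "Table 1: Recruitment schema for Part I", lists participants 1 to 10 by number against five visits. Participants 1-2 are untreated at visit 5, 3-4 at visit 4, 5-6 at visit 3, 7-8 at visit 2 and 9-10 at visit 1. The text adds that "Two participants per visit will receive no nicotinamide" and gives the reason: "This will allow within-participant comparisons and control for the study procedures". Section 7.9 refers the dose at each visit back to the same schema.

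The D5 column is 8 g, "Maximum Tolerated Dose (MTD) or dose found in visits 1-4 capable of upregulating FXN by at least 5-fold".

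On size, the synopsis says "A minimum of ten up to a maximum of 20 FRDA participants will participate in each part of the study". Table 1 has rows for ten.

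Section 11.3.4 uses a screening number and a participant number as identifiers, without saying how or when either is given out. The synopsis describes a pre-post design without comparator therapy, and section 10 bases the evaluation on within-participant change from baseline. The only mention of randomisation is in exclusion criterion 8 of section 4.5 ("positive pre-randomisation serum pregnancy test"), and no procedure stands behind it.

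**The concern.** Each visit in Part I has eight dosed participants and a named pair of untreated ones. Which pair it is follows from the participant number, in an open part whose table is in the protocol. Whoever gives out the next number can therefore know which visit will be untreated and which dose column will be skipped. FXN and SARA are measured at screening (sections 4.1 and 7.8). If the participant number follows screening, which the separate screening number suggests but the protocol does not state, that person may also know the baseline FXN and disability of the participant being numbered.

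Four results could then depend on who holds which number:

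- **Treated versus untreated at one visit.** This contrast is eight people against a known pair, and controlling for procedures is a stated purpose of the untreated visits.
- **Chromatin at visit 5.** Sections 7.6 and 12.1 schedule Part I dosing-visit chromatin at visit 5 only. Under that schedule participants 1-2 are the only untreated chromatin controls, and the procedural control is wholly between participants. Section 7.9 ties the sample to the last dosing visit, which leaves participants 1-2 unclear.
- **Response proportions.** Section 4.1 ends escalation on, among other criteria, a five-fold rise in half of participants.
- **Contrasts between dose levels.** The dose groups are not the same people.

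**Working it through.** **Inputs.** Untreated visit by participant number: Table 1. Two untreated per visit: section 4.1. The protocol gives no SD, power calculation or effect size, so sizes are in between-participant SD units and a normal distribution is assumed.

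**1. The plan's own figure.** Counting Table 1:

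| Visit / dose column | Treated | Untreated |
|---|---|---|
| 1 / D1 | 8 | 9, 10 |
| 2 / D2 | 8 | 7, 8 |
| 3 / D3 | 8 | 5, 6 |
| 4 / D4 | 8 | 3, 4 |
| 5 / D5 | 8 | 1, 2 |

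This reproduces the stated two untreated per visit. Each participant appears once in the last column.

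**2. Overlap of dose groups.** Each column leaves out a different pair, so any two share 10 − 2 − 2 = 6 participants, out of 8 in each. A plain comparison of two dose means is partly between participants.

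**3. Size in the D5 mean.** The simulated expected order statistics of ten standard normal values have −1.538 and −1.000 as the lowest two. If those two hold numbers 1-2, and the ten values sum to zero in expectation, the other eight average (1.538 + 1.000)/8 = 0.317. Direct simulation gave 0.319. The upper bound is therefore about 0.32 SD, and the lower end of the range is 0.

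**4. Size in D5 minus D1.** If participants 9-10 exceed participants 1-2 in mean response by Δ, the unadjusted contrast shifts by (2/8)Δ = 0.25Δ. With the two lowest at 1-2 and the two highest (1.002 and 1.539) at 9-10, the shift is (2.538 + 2.541)/8 = 0.63 SD. This too is an upper bound.

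**5. Size in treated versus untreated at one visit.** If the untreated pair are the two highest, their mean is (1.002 + 1.539)/2 = 1.27 and the other eight average −2.541/8 = −0.32. The gap is about 1.6 SD, again an upper bound. It applies to an uncorrected contrast; subtracting each person's pre-dose value removes stable differences in level.

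**6. Response proportions.** Assume that the denominator is the eight dosed at the visit (the protocol does not say) and that 4 of 10 would respond, a true 40%. If two non-responders sit out, the result is 4/8 = 50%. If two responders sit out, it is 2/8 = 25%. Correcting for each participant's own baseline does not change this.

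**7. Effect of random rows.** There are 10!/(2!)^5 = 3,628,800/32 = 113,400 distinct assignments. The chance of foretelling the first participant's untreated visit falls from certainty, once the number is known, to 2/10 = 20%. Two given participants land together in one given pair of rows with probability 1/C(10,2) = 1/45 = 2.2%. The expected D5-minus-D1 shift becomes 0. Its chance SD is √(4/64) = 0.25 between-participant SD.

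**The case against.** The strongest reply is that the design already limits the harm. Every participant has exactly one untreated visit, so the untreated pool as a whole is all ten people and cannot be selected. Eight of ten are scheduled for D5. The synopsis and section 10 plan within-participant comparisons, so differences in baseline FXN cancel. Restricting a dose contrast to the six shared participants removes the participant main effect. Nobody has reported how this population responds (section 8 calls this the first use in FRDA), so steering numbers towards good or bad responders would be guesswork. All of this stands and narrows the point. It does not cover contrasts at a single visit, the visit 5 chromatin control, proportions among those dosed, or differences in response between unequal dose groups.

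A reader might infer more than the documents support:

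- **That the control group or the top-dose group can be picked outright.** Only who is untreated when, and which two miss the D5 column, is open to choice.
- **That participants 1-2 never receive the D5 dose.** Because D5 may be the MTD or an effective dose from visits 1-4, they may already have had it. The inference is certain only if D5 is a new level.
- **That tolerability at D5 would be badly misread.** If both nausea-prone participants of ten held numbers 1-2, D5 would show 0/8 against 2/10. Those two are scheduled for D1 to D4, however, so susceptibility could show earlier. Neither 0% nor 20% reaches the more-than-half vomiting criterion in section 8.1.
- **That numbers are in fact steered.** Nothing in the protocol says so. The randomisation wording in section 4.5 may be leftover text.

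**Conclusion.** The point holds in limited form, as a cheap improvement. Part I assigns sequences by participant number without a random or concealed step and without a rule for giving out numbers. The protocol settles this in Table 1 itself; it is not a matter left to an analysis plan. The consequence is confined to the four results listed in the concern. For the D5 mean the bias lies between 0 and about 0.32 between-participant SD. The upper end requires the two lowest responders of ten to hold exactly numbers 1-2, and the protocol gives no evidence that numbering tracks response. The larger bounds for D5 minus D1 (0.63 SD) and for one visit's treated-versus-untreated contrast (1.6 SD) rest on similarly extreme placement. Random rows would not cure the main interpretive limit of Part I: each dose column is given at one visit only, so dose stays aliased with visit.

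**What to change.** Keep Table 1 as it is. In section 4.1 and below the table, state that participants are assigned to its rows from a concealed random permutation, prepared by the Imperial CRF statistician mentioned in the synopsis, with each row released only after eligibility is confirmed. State that a second permutation of the same ten rows serves participants 11-20, for whom Table 1 has no rows, and that the count of two untreated per visit applies to each set of ten. Reconcile the wording in exclusion criterion 8 of section 4.5 with whatever procedure is adopted.

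The cost is a short addition to the text and one list. No dose, visit or participant count changes. The small downside is that the investigator can no longer choose the untreated visit for convenience. Because the part is open and the list is finite, the last rows become easier to guess as the others are used. Protection is strongest early in the list.

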**Table 1: Recruitment schema for Part I**

|                | Visit 1 | Visit 2 | Visit 3 | Visit 4 | Visit 5 |
|----------------|---------|---------|---------|---------|---------|
| Participant 1  | D1      | D2      | D3      | D4      | No      |
| Participant 2  | D1      | D2      | D3      | D4      | No      |
| Participant 3  | D1      | D2      | D3      | No      | D5      |
| Participant 4  | D1      | D2      | D3      | No      | D5      |
| Participant 5  | D1      | D2      | No      | D4      | D5      |
| Participant 6  | D1      | D2      | No      | D4      | D5      |
| Participant 7  | D1      | No      | D3      | D4      | D5      |
| Participant 8  | D1      | No      | D3      | D4      | D5      |
| Participant 9  | No      | D2      | D3      | D4      | D5      |
| Participant 10 | No      | D2      | D3      | D4      | D5      |

No = No treatment

D1 = 2g of Nicotinamide

D2 = 4g of Nicotinamide

D3 = 6g of Nicotinamide

D4 = 7g Nicotinamide

D5 = 8g of Nicotinamide , Maximum Tolerated Dose (MTD) or dose found in visits 1-4 capable of upregulating FXN by at least 5-fold.

## **2) Multiple dose study, (Parts II and III)**

There will be two parts to the multiple dose study. Both parts will be pursued following the completion of the single-dose study. There will be at least a one week washout for participants having participated in Part I and going into Part II.

### **Evaluation of the effect of daily dosing for a period of five days, Part II**

Part II of the study will enable an evaluation of the effect of daily dosing for a period of five days to determine whether FXN is upregulated in a sustained manner.

Participants will be admitted to the Imperial CRF for four nights. It may be possible for some participants to return home every evening. This would need to be agreed by the CI.

To enable within participant comparisons, where possible, this study will be performed on the same participants already recruited for the single dose escalation part. If required, additional participants will undergo screening and if eligible may enter directly into this part of the study. The ratio of participants that will be 'on no treatment' to those on 'on treatment' will be 1:4 (i.e one patient will be on 'no treatment' to 4 'on treatment'). Participant's allocation to no drug will be determined at the CI's discretion and discussed and agreed with the participant.

Participants will be treated with 3.5 grams of nicotinamide on the first day. On subsequent days the dose will be escalated to MTD but not higher than 4 grams on day two, 5 grams on day three and 6 grams on days four and five. The daily dosing regimen may be modified at the CI's discretion on clinical grounds. The daily dosing regimen may also be modified from once to twice a day for some participants at the CI's discretion on clinical grounds. Dose escalation will occur only in the absence of AEs that, in the opinion of the CI or his delegates, may put the safety of the participant at risk. If the MTD is reached in one or more participants at any time during the 5-day treatment period, the dose escalation schedule may be adjusted in all the remaining participants to prevent the occurrence of AEs (e.g. excessive nausea, vomit etc) that may put the safety of the participant at risk. In order to avoid nausea, participants will be administered anti-nausea treatment if required (domperidone, 20 mg oral or metoclopramide) prophylactically prior to dosing and post-dosing (domperidone, 20 mg oral up to four times daily; metoclopramide 10-20 mg IV/orally *Pro re nata* [(PRN) up to three times daily]. Participants and their carers will complete Part II of Friedreich's Ataxia Rating Scale (FARS) which is a subscale that measures ADL (Appendix 3) in participants with Friedreich's ataxia. In addition neurological assessments such as SARA and SpinoCerebellar Ataxia Functional Index (SCAFI) scales (Appendices 1 and 2) and a clinician- and/or software-based speech dysarthria assessment will also be performed on day 1 (to count as baseline measurement) and day 5.

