**Comparator therapy, dose and mode of administration:**

No comparator therapy will be used in this study (pre-post therapy study design).

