#### **7.10. Multiple dose study**

##### **Part II**

The multiple dose study is similar to the single dose study and will commence after a washout interval of at least one week.

- Participants will be admitted for four nights within the Imperial CRF and return home after the last blood test on day 5. It may be possible in certain exceptional circumstances for some participants to return home every evening. This would need to be agreed by the CI.

- The ratio of participants that will be 'on no nicotinamide' to those on 'on nicotinamide' will be 1:4 (i.e one patient will be on 'no treatment' to 4 'on treatment'). Participant's allocation to no drug will be determined at the CI's discretion and discussed with the participant. The daily dosing regimen may be modified at the CI's discretion. The daily dosing regimen may be modified from once to twice a day for some participants at the CI's discretion.
- Vital signs assessment (pulse rate, BP, respiration rate, pulse oximetry and temperature) will be repeated prior to each blood sample being taken.
- ECG will be taken predose on day 1 and prior to discharge on day 5.
- Assessment and recording of AEs from baseline throughout the visit
- Review of concomitant medications
- In order to avoid nausea, participants will be administered anti-nausea treatment if required (domperidone, 20 mg oral, metoclopramide etc) prophylactically pre-dose and post-dose (domperidone, 20 mg oral up to four times daily; metoclopramide 10-20 mg IV PRN up to three times daily etc).
- If participants experience nausea they will be given a VAS to rate the severity.
- Blood samples for clinical chemistry, haematology will be taken daily immediately prior to dosing.
- Blood samples to assess FXN level will be taken daily pre-dose and at 2 ( $\pm$  15 mins), 4 ( $\pm$  25mins), 8 ( $\pm$  1) hrs following nicotinamide administration. The pre-dose sample will also represent the 24 hour sample of the previous day. The last 24 hour sample will be taken on day 4. On the last day, the last 8hr PK sample may be taken ( $\pm$ 2)hrs as the Imperial CRF closes at 6pm on Fridays.
- Further blood samples for the chromatin immunoprecipitation will be taken at pre-dose on day 1 and day 5.
- Participants and their carers will complete Part II of FARS. Neurological assessment (SARA and SCAFI scales) and a clinician- and/or software-based speech dysarthria assessment will also be performed on day 1 and day 5.

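### Part II untreated participants are picked at the Chief Investigator's discretion, so any treated-versus-untreated contrast is open to selection bias

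*Protocol*

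**What the plan says.** Section 4.1, under Part II, creates an untreated group: "The ratio of participants that will be 'on no treatment' to those on 'on treatment' will be 1:4". It then says who decides its membership: "Participant's allocation to no drug will be determined at the CI's discretion and discussed and agreed with the participant". Section 7.10 repeats this with one small difference, since the participant's agreement is no longer mentioned: "Participant's allocation to no drug will be determined at the CI's discretion and discussed with the participant".

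Other passages that bear on the point:

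- Size. The Synopsis states: "A minimum of ten up to a maximum of 20 FRDA participants will participate in each part of the study".
- Who enters. Section 4.1 says that, where possible, "this study will be performed on the same participants already recruited for the single dose escalation part". Additional participants may enter directly after screening.
- Measurements. In Part II, FXN is sampled daily. FARS Part II, SARA, SCAFI and a speech assessment are "performed on day 1 (to count as baseline measurement) and day 5".
- Declared design. The Synopsis states: "No comparator therapy will be used in this study (pre-post therapy study design". The Synopsis analysis paragraph and Section 10 describe within-participant comparisons and fold-change from baseline.
- Part III. Everyone, including those untreated in Part II, is offered drug, so there is no untreated group there.

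No selection criteria, random element or concealment is described for Part II.

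**The concern.** Part I builds its control into each person: Table 1 gives every participant one untreated visit. Part II does not. A participant is on drug or off drug for the whole five days, so the untreated data can only be used by comparing different people.

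That comparison has a real job. A before-after change over five days can contain drift in FXN, effects of admission and repeated blood sampling, and practice or learning on SARA, SCAFI and FARS. Adverse events may also have nothing to do with the drug. Within the multiple-dose parts, only the untreated participants show what happens concurrently without drug.

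Part II starts after the single-dose study is complete. For anyone carried over, the person choosing may therefore know that participant's FXN response at several doses, nausea scores and other adverse events. These are the quantities Part II sets out to study. Someone who responded little, tolerated the drug poorly or was less keen could be steered to no drug, in either direction and without any such intention being recorded. A difference between the groups would then mix drug effect with selection.

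**Working it through.** The protocol gives no sample-size, alpha or power figure, so there is no stated result to reproduce. What follows is illustrative. Two-sided 0.05, 80% power and the correlations are assumptions.

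**Group sizes.** A 1:4 split of 10 to 20 participants gives 2 versus 8 up to 4 versus 16.

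**Precision under random allocation.** In SD units of the change score, the standard error of the difference is sqrt(1/c + 1/t), with c untreated and t treated.

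- 2 versus 8: sqrt(1/2 + 1/8) = 0.79 SD. Detectable difference (1.96 + 0.84) × 0.79 = 2.2 SD.
- 4 versus 16: sqrt(1/4 + 1/16) = 0.56 SD. Detectable difference (1.96 + 0.84) × 0.56 = 1.6 SD.

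With 2 versus 8 there are C(10,2) = 45 possible assignments, so the smallest two-sided permutation p-value is 2/45 = 0.044. Random assignment is what would justify that test.

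**Effect of selection.** Let x be whatever guides the choice (for example Part I response) and y the Part II change, with correlation rho and no drug effect. The untreated are the 2 of 10, or 4 of 20, with the lowest x. A two-sample t-test, which is a two-group ANOVA, is run in 20,000 simulated trials per row.

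| Allocation | 2 vs 8: spurious difference | 2 vs 8: false positives | 4 vs 16: spurious difference | 4 vs 16: false positives |
|---|---|---|---|---|
| Random | about 0 | 4.6% | about 0 | 4.8% |
| Selected, rho 0.2 | 0.32 SD | 6% | 0.33 SD | 9% |
| Selected, rho 0.3 | 0.48 SD | 8% | 0.50 SD | 14% |
| Selected, rho 0.5 | 0.80 SD | 15% | 0.83 SD | 32% |

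If rho is 0, selection on x does not bias the change, however it is done. When rho is not 0, the spurious difference does not shrink as the study grows. The standard error does, from 0.79 to 0.56 SD, and so the false-positive rate rises with the larger sample.

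The simulation ranks strictly on x. Looser discretion would give a smaller bias for the same rho. Nothing in the protocol fixes rho or its sign.

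**The case against.** The best reply is that this is declared a pre-post study. FXN fold-change is measured against each participant's own baseline, day 1 is the stated baseline for the clinical scales, and no between-group test for Part II is written down. The Part II paragraph that sets the 1:4 ratio itself begins from within-participant comparison. This stands as far as the primary measure goes: the choice of who is untreated does not alter a treated person's own fold-change. It does not dispose of the point. With no crossover in Part II, the untreated participants cannot serve a within-participant comparison between drug and no drug, so the contrast between people is what they can add.

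A second reply is that randomising two people achieves little, because chance imbalance (0.79 SD) is as large as the assumed bias. This stands in part. Randomisation removes the systematic component and makes the expected difference zero, but it does not make 2 versus 8 informative.

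A reader might infer several stronger claims that the protocol does not support:

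- That the contrast decides whether Part III opens. Sections 4.1 and 7.10 make Part III depend on tolerability and observed FXN changes, and do not mention the untreated group.
- That the bias is about 1.6 SD. This is the expected gap if the two most extreme of ten are chosen, and it is a gap in the selection variable. It carries into change from baseline only in proportion to rho.
- That the rows of Table 1 also need randomising. Table 1 fixes the untreated visits in Part I, and no discretionary assignment to rows is stated.
- That the words "positive pre-randomisation serum pregnancy test" in Section 4.5 show an intended randomised design. They describe the timing of a pregnancy test, and the slip is clerical.

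**Conclusion.** The rule in Sections 4.1 and 7.10 leaves any Part II treated-versus-untreated contrast open to selection bias of unknown size and direction. The protocol does not show that bias will occur. The untreated group is the only concurrent control in the multiple-dose parts. Part I has its own untreated visits, so the point does not extend to the whole study.

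If the basis for selection correlates 0.2 to 0.5 with Part II change, the spurious difference is about 0.3 to 0.8 SD, with false-positive rates of 6 to 15% (2 versus 8) or 9 to 32% (4 versus 16), against about 5% under random allocation. If the correlation is zero there is no bias. These figures rest on assumed correlations, strict ranking and a two-sided 0.05 test.

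The primary FXN fold-change stands. This is a design weakness worth correcting because it is cheap to correct. It does not invalidate the study.

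**What to change.** In Sections 4.1 and 7.10, replace the sentence on discretion with text to this effect: participants are allocated to no drug at 1:4 from a concealed random list held by the Imperial CRF statistician, and the draw is made only after the participant has consented to either allocation and the CI has confirmed fitness for either. Draw whole groups of five together, or vary the block size. In an open-label study with fixed blocks of five, the remaining allocations are known once the untreated place is taken. State that the treated-versus-untreated contrast is descriptive.

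The cost is a list and a sentence, and the Synopsis already names an Imperial CRF statistician as adviser. The CI gives up the choice of who goes untreated, and a participant unwilling to be drawn is not entered. Drawing groups of five means waiting until five are ready. Chance imbalance remains with 2 to 4 untreated participants. The offer of Part III to everyone need not change.
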